### Sample size calculation

2.8

The sample size for this prospective single-arm study was determined based on the primary outcome of the change in the CARS score from baseline to 12 months post-intervention. The calculation is based on the 12-month follow-up data from a large-scale preliminary study by Ye et al. (2022) on FMT for children with ASD (31).

In that study, the mean CARS score in children with ASD before treatment was 35.2 ± 6.5. Following FMT, the mean score at 12 months post-treatment was 31.0 ± 6.7. This represents a mean reduction (δ) of 4.2 points, which is considered the clinically significant difference to be detected in this protocol.

The standard deviation of the difference (*σd*) is required for the calculation. Assuming a conservative correlation coefficient (*r*) of 0.5 between baseline and 6-month measurements (a common assumption for pre-post study designs), the standard deviation of the difference can be estimated using the formula:$$\sigma_{d}=\sqrt{\sigma_{\;pre}^{2}+\sigma_{\;post}^{2}-2r\sigma_{\;pre}\sigma_{\;post}}$$This yields an estimated *σd* of approximately 6.60.

Using a two-sided paired *t*-test, with a significance level (*α*) of 0.05 and a desired statistical power (1-*β*) of 80% $\left(Z_{\beta }=0.8416\right)$, the required sample size (*n*) was calculated using the following formula: $n=(Z_{\alpha /2}+Z_{\beta }{)}^{2}\sigma_{d}^{2}/\delta^{2}$.Therefore, *n* = [(1.96 + 0.8416)^2^ × 6.60^2^]/(4.2^2^) ≈ 19.4.

Based on these parameters, the minimum required sample size is calculated to be 20 participants.

To account for a potential dropout rate of approximately 20% during the 6-month follow-up period, the sample size needs to be adjusted.

Adjusted sample size = *n*/(1—dropout rate) = 20/(1–0.20) = 25.

Therefore, the planned enrollment of 30 participants is more than sufficientto provide adequate statistical power for evaluating the primary outcome of this study.

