### Study design

2.2

This is a prospective, open-label, single-arm, single-center clinical study enrolling children aged 2–12 years with moderate-to-severe ASD. The study aims to evaluate the efficacy and safety of FMT in ASD, investigate microbial colonization patterns, and identify core microbiota post-FMT. Findings will provide evidence-based support for clinical protocols and theoretical foundations for individualized precision therapy in ASD. A technical route map for the study is shown in Figure 1. All clinical data will be recorded on standardized Case Report Forms (CRFs) and entered into a secure, password-protected electronic database to ensure data quality and integrity.

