#### Inclusion criteria

2.3.1

Participants must meet all of the following criteria:
Aged 2–12 years.Diagnosed with ASD according to the Diagnostic and Statistical Manual of Mental Disorders, Fifth Edition (DSM-5), with a CARS total score ≥36 (moderate-to-severe autism).DSM-5 Diagnostic Criteria for ASD:
Onset in early developmental stages.Persistent deficits in social communication and interaction across multiple contexts, accompanied by restricted, repetitive patterns of behavior, interests, or activities.Symptoms cause clinically significant impairment in social, occupational, or other critical functional areas.Symptoms are not better explained by intellectual disability or global developmental delay.CARS Scoring System:
Total score <30: non-autistic.Total score 30–36: mild-to-moderate autism.Total score ≥36: moderate-to-severe autism.Legal guardians fully comprehend the trial's informed consent and voluntarily provide written consent.Compliance with follow-up visits, examinations, and specimen collection.No probiotic supplements consumed within the preceding 3 months.Participants on stable doses of psychopharmacological medications for at least 3 months prior to enrollment are eligible. No new psychopharmacological therapies may be initiated, and no dose changes are permitted during the study period.

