### Outcome measures

2.5

The schedule for all assessments is detailed in Table 1.

**Table 1 T1:** Visit schedule.

Time Window	Within 1 month pre-FMT (Baseline)	FMT treatment period*	1 week post-FMT	2 weeks post-FMT	3 weeks post-FMT	4 weeks post-FMT (±3 days)	5 weeks post-FMT (±3 days)	6 weeks post-FMT (±3 days)***	3 months post-FMT (±3 days)	6 months post-FMT (±3 days)	9 months post-FMT (±3 days)	12 months post-FMT (±3 days)***
Informed Consent	√											
General Data Collection	√	√										
Medical History Collection	√											
Vital Signs, Height, Weight	√	√	√	√	√	√	√	√	√	√	√	√
Inclusion/Exclusion Criteria	√											
Lab Tests**	√	√						√				√
Adverse Event Documentation		√	√	√	√	√	√	√	√	√	√	√
GSRS, DSR	√	√	√	√	√	√	√	√	√	√	√	√
CARS, SRS, ABC	√								√	√	√	√
Recipient Fecal Collection	√	√	√	√		√			√	√	√	√
Donor Fecal Collection	√											

* FMT treatment period: Includes 3 FMT administrations on Day 1, Day 3, and Day 5.

** Lab tests: Baseline tests include routine blood, urine, and stool tests, liver function (ALT, AST), renal function (BUN, Creatinine), coagulation profile, and ECG. Follow-up labs at 6 and 12 months will monitor long-term safety, including: (1) Immune/Inflammatory parameters (CBC with differential, hs-CRP, ESR) and (2) Metabolic parameters (Fasting Glucose, HbA1c, Fasting Lipid Profile, Liver Function Panel, Renal Function Panel).

*** Long-term safety & efficacy follow-ups will specifically monitor long-term safety, including immune, metabolic, and neurodevelopmental parameters.

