#### Primary outcomes

2.5.1

1. **GSRS.**
a.**Timeframe**: Pre-FMT, during FMT, and at 1, 2, 3, 4, 5, 6 weeks, 3 months, 6 months,9 months and 12months post-FMT.b.**Description**: A 15-item questionnaire evaluating GI symptom severity. Each item is scored from 1 (“none”) to 7 (“very severe”), with descriptors: 1 (none), 2 (mild), 3 (slight), 4 (moderate), 5 (marked), 6 (severe), 7 (very severe). Participants with <50% reduction in mean GSRS scores are classified as non-responders.**2. CARS**
a.**Timeframe**: Pre-FMT, 3 months, 6 months,9 months and 12 months post-FMT.b.**Description**: Administered by trained assessors, this 15-item scale yields a total score ranging from 15 to 60. Scores are interpreted as: <30 (non-autistic), 30–36 (mild-to-moderate autism), and ≥36 (moderate-to-severe autism).

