#### Analysis of clinical outcomes

2.7.1

Analysis of clinical data (CARS, GSRS, SRS, ABC) will be conducted using SPSS 26.0. Continuous variables will be expressed as mean ± standard deviation. For comparisons between baseline and specific follow-up points, paired *t*-tests or Wilcoxon signed-rank tests will be used, as appropriate based on data distribution. To analyze the longitudinal changes in primary and secondary outcomes over the multiple time points, linear mixed-effects models will be employed to account for intra-subject correlations.

To ensure the highest standard of statistical analysis, we have formally engaged a qualified statistician as a consultant for this study. The statistician will be involved in the final data analysis plan, execution, and interpretation of results.

The primary analysis of clinical outcomes will be conducted on the per-protocol (PP) population, defined as all participants who complete the primary endpoint assessment at 12 months. A secondary analysis will be performed on the intent-to-treat (ITT) population, which includes all enrolled participants who have received at least one Fecal Microbiota Transplantation administration. For longitudinal data (e.g., GSRS), linear mixed-effects models are inherently robust to data missing at random. For missing primary endpoint data (e.g., 12-month CARS), multiple imputation techniques will be explored and applied if necessary, under the guidance of our study statistician.

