## Discussion

3

ASD constitutes a complex neurodevelopmental disorder with an escalating global prevalence, representing a critical public health challenge. Up to 90% of children with ASD exhibit comorbid GI symptoms which correlate with ASD severity and may exacerbate symptoms through bidirectional interactions with gut microbial dysbiosis.

The MGBA has emerged as a pivotal focus in ASD pathogenesis. Evidence confirms substantial intestinal dysbiosis in ASD populations. FMT is an innovative therapeutic strategy that offers novel potential for ASD intervention by reconstructing the gut ecology. Preliminary studies demonstrate FMT's capacity to reduce ASD and GI symptom scores and sustain improvements in microbial diversity.

However, critical translational barriers persist, including inconsistent efficacy, safety uncertainties, and unclear mechanisms. This prospective single-center single-arm interventional study addresses these gaps by evaluating multi-course FMT efficacy and safety in moderate-to-severe ASD children.

The study has some limitations. As a single-arm, open-label trial, this study cannot completely exclude the potential influences of placebo effects, natural disease progression, or observer bias. This design was chosen with reference to previous foundational studies in the field, such as Kang et al. (29), which utilized a similar open-label approach to provide the first critical evidence of FMT's efficacy. This study is intended as an exploratory trial to provide preliminary evidence and valuable data from the Chinese population, which will be invaluable for designing future large-scale, placebo-controlled trials. The absence of healthy controls also limits clinical benchmarking. Furthermore, the use of a single donor, while a deliberate choice to minimize inter-donor variability as a confounding factor in this preliminary efficacy study, may limit the generalizability of the findings, as the concept of an “ideal donor” is still under investigation.

To counterbalance these limitations, the protocol incorporates rigorous safety oversight via an independent DSMB and extends follow-up to 12 months to assess long-term outcomes. Additionally, the employment of deep mNGS will provide high-resolution insights into microbial engraftment and functional pathways.

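### Entry requires CARS ≥36 and change from what appears to be that same score is tested against zero in one arm, so part of any fall will be regression to the mean, which the protocol neither names nor allows for

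*Protocol article*

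**What the plan says.** - **Selection.** Section 2.3.1 requires a DSM-5 diagnosis "with a CARS total score ≥36 (moderate-to-severe autism"). Section 2.4.2 repeats the cut-off.
- **Baseline.** Table 1 has one pre-treatment column, "Within 1 month pre-FMT (Baseline"), which holds both the eligibility check and the only pre-FMT CARS. Section 2.5.1 gives the CARS time points as "Pre-FMT, 3 months, 6 months,9 months and 12 months post-FMT". No second pre-treatment CARS is scheduled.
- **Design and test.** The trial is a "prospective, open-label, single-arm, single-center clinical study". Section 2.7.1 states: "For comparisons between baseline and specific follow-up points, paired *t*-tests or Wilcoxon signed-rank tests will be used". Linear mixed models are added for the repeated measurements.
- **Planning figures.** Section 2.8 takes its effect from a cited FMT cohort: "the mean CARS score in children with ASD before treatment was 35.2 ± 6.5", falling to 31.0 ± 6.7 at 12 months. The 4.2-point difference becomes the target, with an assumed pre-post correlation of 0.5.
- **Limitations.** The Discussion says that the design "cannot completely exclude the potential influences of placebo effects, natural disease progression, or observer bias". Regression to the mean is not named there or elsewhere.

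**The concern.** Children admitted because one score is high will, on average, score lower when next rated, even if nothing about them has changed. When the qualifying score is also the baseline, and the null hypothesis is zero mean change with no control group, that fall counts towards efficacy.

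The planning cohort sharpens the point. Its mean of 35.2 is below the cut-off of 36, so this trial enrols only the upper part of such a distribution, and the 4.2 points do not describe the children who will be enrolled.

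Two uses of the result are at stake. The Introduction hypothesises a significant improvement in core deficits, and section 2.8 sizes the trial for a two-sided 5% test. The Discussion says the trial will supply effect sizes for later randomised trials. An effect inflated by regression would make those trials too small.

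**Working it through.** **1. The plan's own figure.** SD of the difference = √(6.5² + 6.7² − 2 × 0.5 × 6.5 × 6.7) = 6.60. Then n = (1.96 + 0.8416)² × 6.60² / 4.2² = 19.4, rounded up to 20, and 20/0.80 = 25. Section 2.8 reproduces.

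**2. Inputs.** Cut-off 36 (section 2.3.1). Mean 35.2, SDs 6.5 and 6.7, r = 0.5, target 4.2, enrolment 30 and 20% dropout (section 2.8). Enrolment less dropout leaves 30 × 0.80 = 24.

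Assumptions that the protocol does not state: the cited cohort is the population from which children are selected, its scores are normal, and r applies without treatment.

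**3. Who is selected.**
- a = (36 − 35.2)/6.5 = 0.123
- Share at or above 36: 1 − Φ(a) = 0.451
- λ = φ(a)/(1 − Φ(a)) = 0.878
- Expected baseline mean = 35.2 + 6.5 × 0.878 = 40.9, or 5.71 above the source mean
- SD of the selected baseline = 6.5 × √(1 + aλ − λ²) = 3.78

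**4. Fall with no treatment effect.** Fall = (1 − r × SDpost/SDpre) × (baseline mean of selected children − source mean). At r = 0.5:
- Slope = 0.5 × 6.7/6.5 = 0.515
- Fall = (1 − 0.515) × 5.71 = 2.77 points, that is from 40.9 to 38.1
- 2.77/4.2 = 66%
- SD of change = √((1 − 0.515)² × 3.78² + 6.7² × (1 − 0.5²)) = 6.08

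**5. Chance that the two-sided 5% paired t-test rejects with no treatment effect** (noncentral t), using the same formula throughout:

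| Source mean | r | Fall (points) | Share of 4.2 | Rejection, n = 24 | Rejection, n = 30 |
|---|---|---|---|---|---|
| 35.2 | 0.5 | 2.77 | 66% | 57% | 67% |
| 35.2 | 0.7 | 1.59 | 38% | 33% | 40% |
| 35.2 | 0.8 | 1.00 | 24% | 21% | 26% |
| 35.2 | 0.9 | 0.41 | 10% | 10% | 12% |
| 40 | 0.5 | 1.42 | 34% | 19% | 23% |
| 40 | 0.8 | 0.51 | 12% | 9% | 10% |

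With equal SDs of 6.5, the fall at mean 35.2 and r = 0.5 is 2.85 points (68%). A simulation of that case gave 2.84.

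**6. Is the first row a ceiling?** No. A source mean of 33 at r = 0.5 gives a fall of 3.5 points (83% of 4.2). A correlation of 0.4 at mean 35.2 gives 3.35 points (80%).

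**The case against.** **The size rests on borrowed inputs. This stands.** The protocol does not say that the cited cohort was unselected, normal, or like the children screened at this hospital, and gives no CARS distribution for the latter. Section 2.8 presents r = 0.5 as a cautious planning value, which suggests that the true correlation may be higher. It is also meant for treated children, whose correlation may be lowered by variable response. A reader might infer that regression to the mean explains two thirds of the target, or at most two thirds. Neither follows: other plausible inputs give less and some give more.

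**That the entry score is the baseline is inferred. This stands in part.** Section 2.4.2 ties diagnosis to a physician, while section 2.5.1 has CARS given by trained assessors, so an earlier diagnostic score may exist. But only one pre-FMT CARS is scheduled, and no sentence separates the two roles.

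**The limitations already concede the point. This stands only in part.** They admit three uncontrolled influences and call the trial exploratory. Regression to the mean is a different mechanism: it comes from the entry rule and would occur with stable disease and a blinded rater. Unlike the other three, it can be given an approximate size within a single arm.

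**The mixed models deal with it. This does not stand.** Section 2.7.1 adopts them for correlation within a child. That alone does not remove selection on the outcome from a change measured within one group.

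**Conclusion.** The concern holds in a limited form. Selection on CARS, a single scheduled pre-FMT CARS and a test against zero in one arm mean that part of any observed fall will be regression to the mean, and the plan as written would count it as efficacy.

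The size is uncertain. With the cited cohort as a normal source population, the fall with no treatment effect runs from about 2.8 points at r = 0.5 to 0.4 at r = 0.9. With a source mean of 40 and r = 0.5 to 0.8 it is 1.4 to 0.5 points. In every row of the table the false-positive rate is about twice the nominal 5% or more. That a problem exists therefore does not depend on the worst case, but its seriousness does.

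A reader might also infer that the sample size is miscalculated or the trial underpowered. The documents do not support this: the arithmetic in section 2.8 is right, and the SD of change after selection at r = 0.5 (6.08) is below the planned 6.60. The GSRS, the other primary outcome, has no entry cut-off, so this point does not apply to it.

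**What to change.** 1. **Section 2.7.1.** Pre-specify a sensitivity analysis that sets the mean CARS reduction and its 95% CI beside the expected regression, (1 − r × SDpost/SDpre) × (enrolled baseline mean − source mean). Use r = 0.5 to 0.9 and a plausible range of source means, for example from the CARS scores of all children screened, if recorded. State that a reduction will not be attributed to FMT on a test against zero alone when the CI does not clear that range. A single mandatory benchmark would not be sound, because the source mean is unknown and nothing fixes which r should decide.
2. **Section 2.8.** State that the planning cohort's mean lies below the entry cut-off.
3. **Limitations.** Name regression to the mean.
4. **Optional.** Where an earlier diagnostic CARS already exists, use it for eligibility and the scheduled pre-FMT CARS as the analysis baseline. This reduces the regression but does not remove it. For illustration, assume a one-month reliability of 0.9 and a 12-month r of 0.5 with the qualifying score. Then 0.9 × 5.71 − 0.515 × 5.71 ≈ 2.2 of the 2.8 points remain.

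**Cost.** Items 1 to 3 are wording and analysis only, and item 4 uses scores already held. The downside is that the efficacy claim becomes harder to make. At r = 0.5, source mean 35.2 and n = 24, the observed reduction would have to exceed about 2.77 + 2.069 × 6.08/√24 = 5.3 points for the CI to clear the expected regression.

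### The sample size for a 12-month endpoint uses 6-month dropout and correlation and understates the minimum n (20 instead of 22), so calling 30 children more than enough is unsupported, though not shown to be false

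*Protocol article*

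**What the plan says.** Section 2.8 says the sample size was "based on the primary outcome of the change in the CARS score from baseline to 12 months post-intervention". The 4.2-point effect and both standard deviations (6.5 before treatment, 6.7 after) come from 12-month data in a cited study. Section 2.7.1 makes the per-protocol set primary and defines it as "all participants who complete the primary endpoint assessment at 12 months".

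Two inputs to the same calculation carry a different time label:

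- The correlation of 0.5, which the protocol calls conservative, is described as "between baseline and 6-month measurements (a common assumption for pre-post study designs".
- The attrition sentence reads "To account for a potential dropout rate of approximately 20% during the 6-month follow-up period, the sample size needs to be adjusted".

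The test named is a two-sided paired t-test at 5% with 80% power. The formula used is the normal approximation. It gives a minimum of 20 evaluable children, inflated to 25 for dropout. The section concludes that "the planned enrollment of 30 participants is more than sufficientto provide adequate statistical power".

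**The concern.** The number of children analysed depends on retention to 12 months, and the standard deviation of the change depends on the correlation between baseline and 12 months. The protocol gives neither. If 12-month loss is higher, or the 12-month correlation lower, than the 6-month values, the margin between 25 and 30 may be smaller than it looks or may disappear.

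Separately, the normal approximation is optimistic at about 20 observations, because the t-test has to estimate the variance. The stated minimum could therefore miss its own power target whatever the time labels say.

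This is the only sample-size justification in the protocol. If it overstates the margin, a null 12-month CARS result could be read as coming from a comfortably powered trial.

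**Working it through.** **Inputs, all from section 2.8:** SD before = 6.5; SD after = 6.7; effect = 4.2; r = 0.5; two-sided alpha = 0.05; power = 80%; dropout = 20%; planned enrolment = 30.

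**Step 1. Reproduce the protocol.**
- SD of the difference = √(6.5² + 6.7² − 2 × 0.5 × 6.5 × 6.7) = √(42.25 + 44.89 − 43.55) = √43.59 = 6.60.
- n = (1.96 + 0.8416)² × 6.60² / 4.2² = 19.4, rounded up to 20.
- 20 / (1 − 0.20) = 25.

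All the printed figures reproduce. The problem lies in the choice of inputs and formula.

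**Step 2. Use the test that is named.** Power of the paired t-test comes from the noncentral t distribution with n − 1 degrees of freedom and noncentrality (4.2 / 6.602) × √n:

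| Evaluable n | Power at r = 0.5 |
|---|---|
| 19 | 74.6% |
| 20 | 77.0% |
| 21 | 79.2% |
| 22 | 81.2% |
| 24 | 84.7% |
| 30 | 92.0% |

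The minimum for 80% is 22. Inflated for 20% loss: 22 / 0.80 = 27.5, so 28 enrolled. The margin below 30 falls from five children to two.

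**Step 3. Check 30 enrolled at the stated values.** 30 × 0.80 = 24 completers, with 84.7% power by the paired t-test. So 30 is enough if 20% and 0.5 are the 12-month values.

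**Step 4. Find the largest 12-month loss that 30 can absorb at r = 0.5.** With 22 completers needed, 8 of 30 may be lost: 8 / 30 = 26.7%. By the protocol's own formula, which needs 20 completers, the limit is 10 / 30 = 33.3%.

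**Step 5. Vary what the protocol does not give.** These are assumptions, taken in both directions for r. The SD of the difference is 7.23 at r = 0.4 and 5.91 at r = 0.6. The 19-completer column supposes that 20% is lost in each six months: 30 × 0.80 × 0.80 = 19.2, a 36% loss.

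| r (baseline to 12 months) | Exact n for 80% | Power, 24 completers | Power, 19 completers |
|---|---|---|---|
| 0.4 | 26 | 77.8% | 66.8% |
| 0.5 | 22 | 84.7% | 74.6% |
| 0.6 | 18 | 91.5% | 83.4% |

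With 24 completers, the paired t-test reaches 80% only for r of about 0.44 or more. With 19 completers it needs about 0.57 or more.

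**The case against.** The strongest defence is that the conclusion survives the correction. Enrolment was set at 30, not 25, and 30 exceeds the corrected 28. The effect and both standard deviations are already 12-month values. The correlation of 0.5 is offered as a generic figure, so relabelling it need not change it. The trial calls itself exploratory (section 3). Section 2.7.1 also plans mixed models, an analysis of all treated children and possible multiple imputation, which partly offset losses. All of this stands, and it limits how serious the point is. It does not supply the missing 12-month values, and the primary set remains the 12-month completers.

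A reader might go further and infer that the trial is underpowered because 36% will be lost by month 12. The protocol does not support that. It gives about 20% over a 6-month follow-up. It does not say 20% in every six months, and it states no pattern of loss. Treatment ends on Day 5 and visits are densest in the first six weeks, so early loss is equally possible. Even at 36%, the protocol's own formula gives 79% power.

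A reader might also infer that the 12-month correlation must be below 0.5. Nothing in the document settles the direction. At r = 0.6, even 19 completers give 83% power.

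**Conclusion.** The point holds in a limited form. Two things are wrong on the page. The dropout rate and correlation are stated for 6 months in a calculation for a 12-month endpoint analysed in 12-month completers. The minimum of 20 gives 77% power under the named test, so the figures should be 22 evaluable and 28 enrolled. The second finding needs no assumption beyond the protocol's own inputs.

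What follows for the trial is an unsupported assurance, not a demonstrated power shortfall. Thirty enrolled gives 85% power if 20% loss and r = 0.5 hold at 12 months. At r = 0.5 it keeps at least 80% as long as 12-month loss does not exceed 26.7%. Across the assumed ranges above, power runs from about 67% to 91.5%.

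All of these figures rest on the borrowed standard deviations. In the source study "the mean CARS score in children with ASD before treatment was 35.2 ± 6.5", whereas this trial admits only children scoring 36 or more (section 2.3.1), so the variability here may differ. This should be corrected, but it is no reason to change enrolment.

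**What to change.** Keep 30 enrolled and revise section 2.8:

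1. State the expected dropout and the pre-post correlation for 12 months, with their basis, or say plainly that they are assumptions.
2. Replace 20 evaluable and 25 enrolled with the paired t-test values, 22 and 28 (at r = 0.5 and 20% loss by 12 months).
3. Replace the closing claim with a two-sided power range marked as assumptions: with 24 completers, about 78%, 85% and 91.5% at r = 0.4, 0.5 and 0.6; with 19 completers (if 20% were lost in each six months), about 67%, 75% and 83%.
4. Add that at r = 0.5 the 80% target holds only if 12-month loss is at most 26.7%, and that the standard deviations come from a group with a lower baseline mean than this trial's entry threshold.

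The cost is a text change and a less favourable statement of power. No additional children are needed, and no endpoint, test or analysis set changes.
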